### Rehabilitation

Between the assessment phases, participants will be allocated to a rehabilitation program. It will be different based on the group: 15 days for PD and 4 weeks for anorexia patients.

PD will participate in a daily rehabilitation program from Monday to Saturday including one hour of physical therapy each day. Patients will be guided by a physiotherapist as they complete exercises that improve gait speed, walking ability, and balance. Depending on the patient’s comorbidities, the additional two hours per day may involve one or more of the following activities: rehabilitation psychology, speech and swallow therapy, language therapy, cognition therapy, and therapies oriented toward daily function and community reintegration.

Instead, patients with AN will go through 4 weeks of rehabilitation based on refeeding in a medical setting. The refeeding program is implemented by a multidisciplinary team of doctors, dietitians, educators, and psychologists. The following criteria form the basis of the refeeding strategy: Higher calorie feeding is preferred in moderately malnourished patients with AN; meal-only approaches or combined nasogastric plus meal-feeding approaches are taken into consideration based on patient compliance; higher calorie refeeding strategies appear safe in severely malnourished patients with AN in the presence of medical monitoring and electrolyte correction.

As a crucial step in assisting the refeeding process, the rehabilitation psychology program will be coordinated and supervised by the psychologist with the aid of the educator, with daily individual meetings.

Patients who can support physical activity will go through a standardized rehabilitation program: during these 4 weeks, they will be directed by a physiotherapist through exercises to improve their walking ability and endurance, and balance control an hour a day, from Monday through Saturday. The proposed rehabilitation is an element of clinical routine, and we need to understand whether and how mental flexibility, encoded in its cognitive-affective dimensions, is a trait or state dimension. Patients, after routine rehabilitation performed in the hospital, might have an improvement in the affective-cognitive components of MF [53].

### Timing of the study

The study will take two years to complete, with patient recruitment and data collection taking 18 months, and data analysis and processing taking 6 months. These timelines account for the time required to: enroll patients; administer assessment scales; provide effective therapeutic care; data collection and data analyzing.

### Analysis of biomakers

All endocrinological measures are analyzed in IRCCS Auxologico Piancavallo. Patients will be fasted in the morning between 7.30 and 8.30 am with a sample of 2 serum tubes and 3 plasma tubes for the dosage of interleukin 6, cortisol, serotonin, catecholamines and endorphins.

The samples will be centrifuged and aliquoted at -80 degrees Celsius in order to preserve the analytes that will be dosed. A kit from the company IBL-International called an ELISA will be used to measure the dosages of serotonin, catecholamines, and endorphins. Endocrinological detection will take place on days other than rehabilitation protocol.

### Data collection

The patient data sheet will be filled out with clinical and disease information, including results from instrumental and humoral tests (electronic CRF). Based on the center code and enrollment sequence, an alphanumeric code will be used to identify patients (e.g., PI-001).

### Statistical analysis

The statistical methodology employed in this study centers around a 2x2 univariate analysis of variance (ANOVA) model. In this model, the between-subjects factor encompasses the distinction between patients and controls, while the within-subjects factor is delineated by the acute phase upon hospitalization (T0) and post-rehabilitation (T1). The primary objective of adopting a univariate approach is to systematically assess the effects of both group membership and time on measures of cognitive flexibility and affective flexibility. Furthermore, we seek to investigate potential interaction effects that may exist between these factors (Fig 4).

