### Sample size

The sample size was calculated using Gpower 3.1, separately for PD and AN population class. For eating disorders, the study by Sierra and colleagues [82] was used to estimate effect dimension: in the study, IAPS (International Affective Picture System) results were used as a variable dependent on predictive variables describing the emotionality of patients, such as the PANAS (Positive and Negative Affect Schedule). In order to be more conservative and with an effect size of 0.34 and a statistical power of 0.95, we project about 40 subjects, considering eventually drop-out, for the patient and control groups, respectively.

**F tests—**ANOVA: Repeated measures, within-between interaction

**Analysis:** A priori: Compute required sample size

**Input:** Effect size f   = 0.34

   α err prob   = 0.05

   Power (1-β err prob)   = 0.95

   Number of groups  = 2

   Number of measurements = 2

   Corr among rep measures = 0.5

   Nonsphericity correction ε = 1

**Output:** Noncentrality parameter λ = 14.7968000

   Critical F   = 4.1708768

   Numerator df   = 1.0000000

   Denominator df  = 30.0000000

   Total sample size  = 32

   Actual power   = 0.9608705

The study by Ille and colleagues [83] was used to estimate the effect dimension of PD group: The study used IAPS to investigate patients’ emotional reactions. In order to be more conservative and with an effect size of 0.39 and a statistical power of 0.95, we project about 30 subjects, considering eventually drop-out, for the patient and control groups, respectively.

**F tests—**ANOVA: Repeated measures, within-between interaction

**Analysis:** A priori: Compute required sample size

**Input:** Effect size f   = 0.39

   α err prob   = 0.05

   Power (1-β err prob)  = 0.95

   Number of groups  = 2

   Number of measurements = 2

   Corr among rep measures = 0.5

   Nonsphericity correction ε = 1

**Output:** Noncentrality parameter λ = 14.6016000

   Critical F   = 4.3009495

   Numerator df  = 1.0000000

   Denominator df  = 22.0000000

   Total sample size  = 24

   Actual power  = 0.9544574

Control groups will be paired by age and gender relative to patient groups.

Top of Form

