**Fig 4 pone.0293921.g004:**
[figure not shown]
Analysis framework. For each measure of cognitive and affective flexibility an ANOVA 2*2 is implemented with between level of the group (PD/AN vs. Control Group) and within level of time (T0 vs. T1). Then a correlational analysis will be run between cognitive and affective components of flexibility and concurrent measures, considering both T0 and T1 measures.

For assessing Cognitive Flexibility, which involves a diverse array of measurements, we plan to construct a composite score solely relying on self-report data. This composite score will be derived through an Exploratory Data Analysis (EDA) approach employing linear principal component analysis (PCA). By applying PCA, we will extract common underlying dimensions from the various cognitive flexibility self-reports (e.g CFI, CFS, CCFQ, FREE, Dflex) allowing us to aggregate similar items from distinct scales into a weighted average score (Fig 4).

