**Fig 5 pone.0293921.g005:**
[figure not shown]
Markov chain model. From the Core affect model of Russel we can compute 12 complete transitions between affective states, we can insert them in a randomized sequence, calculate transition between blocks and state trait indexes, and once the variability indexes have been relativized, we can fit them into a Markov matrix.

By doing so, we effectively capture the probability of transitioning between and into blocks, empowering to uncover the intricacies of affect dynamics in both music’s auditory realm and images’ visual domain.

From each subject’s data and for each physiological signal, we extracted and analyzed only the main-diagonal indexes, denoted as state trait indexes (AA-BB-CC-DD), which convey the subject’s probability of remaining anchored in a specific affective state (stability).

This meticulous methodology allows us to rigorously assess and understand the dynamics of affective experiences through the lens of Markov chains, offering valuable insights into the temporal evolution of emotional states in our experimental context.

Our anticipated outcomes encompass the following hypotheses:

For participants within the control group, we hypothesize that there will be no statistically significant differences between the scores obtained at T0 and T1, both for measures of cognitive flexibility and affective flexibility. This expectation suggests that individuals in the control group are likely to maintain stable levels of cognitive and affective flexibility over time.Conversely, we expect an interaction effect between group membership (patients) and time (T0 to T1). This interaction effect signifies our hypothesis that cognitive flexibility measures will exhibit improvement over time among patients, leading to concurrent enhancements in affective flexibility. In particular, motor rehabilitation could have a significant impact on executive function, related to mental flexibility, while cognitive-behavioral therapy of individuals with AN could have an impact on both executive function and emotional flexibility.

In essence, our statistical analysis anticipates that patients will demonstrate increased cognitive and affective flexibility throughout the study period.

These hypotheses provide a clear framework for our statistical analysis and offer valuable insights into the expected outcomes of this multifaceted assessment of flexibility.

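### The two-visit 2x2 ANOVA, run as named, discards the T0 data of anyone without T1; a mixed model on all data would avoid a modest bias if drop-out depends on T0 and differs between groups.

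*Protocol article*

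**What the plan says.** The Statistical analysis section opens with: "The statistical methodology employed in this study centers around a 2x2 univariate analysis of variance (ANOVA) model". Patients versus controls is the between factor and T0 versus T1 the within factor. The Fig 4 caption extends this to every outcome: "For each measure of cognitive and affective flexibility an ANOVA 2*2 is implemented with between level of the group (PD/AN vs. Control Group". Among the hypotheses at the end of that section, the central one is the interaction: "we expect an interaction effect between group membership (patients) and time (T0 to T1". The same list also predicts no T0-T1 change in controls and improvement in patients, so within-group change is interpreted as well.

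The Sample size section gives G*Power totals of 32 for anorexia nervosa (AN) and 24 for Parkinson's disease (PD), and raises them to about 40 and about 30, "considering eventually drop-out". It states no drop-out rate. The wording also leaves open whether 40 and 30 are totals or numbers per group.

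Materials and procedure places T1 after 15 days of rehabilitation in PD and 4 weeks in AN. The article does not say what happens to a person who has T0 but no T1.

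**The concern.** A classical repeated-measures ANOVA with two visits amounts, for the interaction, to a comparison of each person's T1 minus T0 between groups. A person without T1 has no difference and drops out. The plan therefore names a method that cannot use the T0 values of people it expects to lose.

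If those who leave were unusually low (or high) at T0, those who stay start above (or below) the group mean. Part of that gap closes by regression to the mean at T1, which shifts the observed change. When this happens more in one group than the other, the shift enters the interaction, which is the key test. When it happens equally in both, it cancels from the interaction but remains in each group's own change. That matters for the prediction of stable controls and for the question, raised in the Rehabilitation section, of whether flexibility is a trait or a state.

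**Working it through.** **1. The plan's own figures.** Inputs from the Sample size section: f = 0.34 (AN) and 0.39 (PD), alpha 0.05, power 0.95, two groups, two measurements, correlation 0.5. The noncentrality is lambda = f² × N × m / (1 − rho), with m = 2 visits.
- AN: 0.34² × 32 × 2 / 0.5 = 14.7968; F with 1 and 30 df; critical F 4.1709; power 0.9609.
- PD: 0.39² × 24 × 2 / 0.5 = 14.6016; F with 1 and 22 df; critical F 4.3009; power 0.9545.

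Both agree with the printed output.

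**2. The planned effect in SD units.** With two groups and two visits, the interaction contrast (difference in mean change) is 4f: 4 × 0.34 = 1.36 SD in AN and 4 × 0.39 = 1.56 SD in PD. Check for AN: the change score has variance 2(1 − 0.5) = 1, so with 16 per group SE = √(2/16) = 0.354, and (1.36/0.354)² = 14.8 = lambda.

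**3. The drop-out allowance.** If 40 and 30 are totals: 1 − 32/40 = 20% and 1 − 24/30 = 20%. If they are per group (80 and 60 in all): 1 − 32/80 = 60% and 1 − 24/60 = 60%. The 20% used below is therefore one reading, taken as an assumption.

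**4. Bias of complete pairs.** Let M be the mean T0 deviation, in SD, of those who stay. Their expected T1 deviation is rho × M, so their mean change is shifted by −(1 − rho) × M. Assume that 20% of patients and no controls are lost, with loss logistic in T0 and likelier at low scores:

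| Log-odds of loss per SD of T0 | M | Shift, rho 0.5 | Shift, rho 0.7 |
|---|---|---|---|
| 0.5 | 0.096 | −0.05 | −0.03 |
| 1 | 0.173 | −0.09 | −0.05 |
| 2 | 0.262 | −0.13 | −0.08 |
| lowest fifth all leave | 0.350 | −0.17 | −0.10 |

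At rho 0.3 and log-odds 1 the shift is −0.7 × 0.173 = −0.12 SD. If high scorers leave instead, the signs reverse.

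**5. Other loss patterns (rho 0.5, log-odds 1 to 2).**
- Loss of 30% in patients and 10% in controls: interaction bias −0.08 to −0.12 SD.
- Loss of 20% in both groups by the same mechanism: interaction bias 0.00, but each group's own change is shifted by −0.09 to −0.13 SD.

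**6. Effect on the test (simulation, patient-only loss of 20%, log-odds 1 to 2).**
- Type I error of the complete-pair test: 0.057 to 0.068 with 20 per group, and 0.066 to 0.084 with 40 per group.
- Power for 1.36 SD with 20 per group: 0.945 to 0.958, against 0.976 when the same loss is random.

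**7. The alternative.** Maximum likelihood on all T0 and T1 data with unstructured covariance has bias 0.00 in the settings of steps 5 and 6. Its standard error is almost the same: with 20 per group, no true effect and log-odds 1, both methods give about 0.334.

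**8. Its limits.**
- With T0-T1 correlations of 0.3 in patients and 0.7 in controls, a pooled covariance leaves −0.04 to −0.07 SD; a group-specific one leaves 0.00.
- With a patient SD of 1.5 at T1, a random-intercept model leaves about +0.05 SD.
- If loss depends on the unseen T1 (20% of patients, log-odds 1, rho 0.5), stayers are high by 0.173 at T1 and 0.5 × 0.173 = 0.087 at T0. Complete pairs are then off by 0.173 − 0.087, about +0.09 SD. The mixed model uses the stayers' slope of T1 on T0 (about 0.46) and is off by 0.173 − 0.46 × 0.087, about +0.13 SD, which is somewhat worse.

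**The case against.** The strongest reply is that the article names a model, not a missing-data policy. A reader might infer that it commits to analysing completers only. It does not say so, and a full protocol or analysis plan that is not shown could specify imputation. That stands: exclusion of incomplete cases is a property of the named method when run as written. The point is therefore about the choice of model, for which a better one costs almost nothing, and not about an absent policy.

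A reader might also infer that 20% drop-out is built in, that it falls mainly on patients, and that controls will be nearly complete. None of this is documented. The rate depends on reading 40 and 30 as totals. Patients stay in hospital for only 15 days or 4 weeks, and nothing is said about how well controls will be retained. Dependence of loss on T0 is likewise an assumption, and its direction is unknown. Without unequal loss (or unequal correlations) between groups, the interaction is not biased.

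Size also counts against a strong claim. A bias of 0.09 SD is about a quarter of the standard error with 20 per group (0.09/0.334 = 0.27), and power remains near 0.95 under the planned effect.

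Finally, the sentence "Control groups will be paired by age and gender relative to patient groups" may tempt a reader to say that the ANOVA wrongly ignores matched pairs. It can equally mean matching at group level. In any case, a pair effect that is constant over visits cancels from each person's change, so it does not bear on the interaction.

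**Conclusion.** The point holds in a limited form. The named ANOVA cannot use people without T1, and the plan expects some. If loss depends on T0 and differs between groups, the interaction is biased by about 0.05 to 0.13 SD, or about 0.17 SD at the extreme, assuming 20% loss in patients only and correlation 0.5. Against the planned 1.36 SD in AN, that is 4% to 10% (0.05/1.36 to 0.13/1.36), or 13% at the extreme (0.17/1.36). The distortion would matter more if true effects are smaller than planned, and it inflates type I error slightly. If both groups lose people alike, only the within-group changes are affected. Neither the presence nor the direction of bias can be established from the article. The reason to act is that the protection is nearly free. A mixed model is not a complete remedy: it depends on loss being explained by observed T0 and on a covariance that fits.

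**What to change.** Analyse each flexibility measure by a linear mixed model with group, visit and group-by-visit as fixed effects, using all available T0 and T1 data. Use an unstructured within-person covariance, group-specific if patients and controls differ in variance or correlation, and avoid a random-intercept-only structure. Keep the complete-pair ANOVA as a sensitivity analysis. Report the number with T1 and the mean T0 score of those with and without T1, by group, and acknowledge that loss depending on the unseen T1 score is not corrected.

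The cost is analysis wording only. With complete data and a pooled covariance, the interaction test is the same as the planned ANOVA, so the sample size calculation is unaffected. It would help to state in the same edit the assumed drop-out rate and whether 40 and 30 are totals or per group.

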**Fig 4 pone.0293921.g004:**
[figure not shown]
Analysis framework. For each measure of cognitive and affective flexibility an ANOVA 2*2 is implemented with between level of the group (PD/AN vs. Control Group) and within level of time (T0 vs. T1). Then a correlational analysis will be run between cognitive and affective components of flexibility and concurrent measures, considering both T0 and T1 measures.

For assessing Cognitive Flexibility, which involves a diverse array of measurements, we plan to construct a composite score solely relying on self-report data. This composite score will be derived through an Exploratory Data Analysis (EDA) approach employing linear principal component analysis (PCA). By applying PCA, we will extract common underlying dimensions from the various cognitive flexibility self-reports (e.g CFI, CFS, CCFQ, FREE, Dflex) allowing us to aggregate similar items from distinct scales into a weighted average score (Fig 4).

In the context of affective flexibility, we will consider transition indicators derived from physiological measuring (ECG, f-EMG, GSR, RSP) and analyzed by the Markov chain models. The choice of Markov chains as our analytical framework stems from their inherent capacity to capture probabilistic transitions between discrete states, a quality that aligns seamlessly with the nuanced shifts and fluctuations observed in affective experiences. By harnessing the capabilities of Markov chains, we dissect the temporal evolution of emotional states and elucidate the underlying patterns that define affective transitions. Our experimental design affords us the opportunity to calculate and evaluate affect variability across different affective transitions, which can subsequently be normalized and integrated into the Markov chains. Initially, we will calculate the reciprocal ratio between the absolute mean and variability of the signal standardized variability measures based on the inverse of Noise to Signal. The standardized variability index is computed for each transition, considering the 30-second interval between blocks (120’’+-15’’) (Fig 5). However, it is also necessary to consider state indexes for each block in the Markov matrix, specifically the transition of state e.g. A to itself, called *state trait transition*. State trait transitions represent the probability of remaining in the same emotional state, and in the Markov Matrix, they are represented as the main diagonal. These state trait indexes are determined during the central 30 seconds of each affective block (from 45 to 75 seconds) Within the Markov matrixes, we will relativize the prior transition variability indexes, to experiment the probability of passing from one affective state to another. Normalization of transition indexes is required because the sum of transitions in Markov matrices is 1.

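### At least 17 group-by-time tests per population with no measure ranked first, while each sample size is computed for one unnamed test at alpha 0.05

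*Protocol article*

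**What the plan says.** The caption of Fig 4 in the Statistical analysis section sets the unit of testing: "For each measure of cognitive and affective flexibility an ANOVA 2*2 is implemented with between level of the group", with time (T0, T1) as the within factor. The self-report flexibility scales are to be merged by principal components into a composite that uses self-report data only, so the neuropsychological tests listed under Assessment stay outside it.

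On the affective side, the text around Fig 5 says that "for each physiological signal, we extracted and analyzed only the main-diagonal indexes". There are four such indexes (AA, BB, CC, DD), and the signals listed are ECG, facial EMG, GSR and respiration. The expected result is a group-by-time interaction on both families, summarised as "our statistical analysis anticipates that patients will demonstrate increased cognitive and affective flexibility throughout the study period". None of the measures is named as primary.

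The Sample size section runs one calculation per population, each for "ANOVA: Repeated measures, within-between interaction" with "α err prob = 0.05" and "Corr among rep measures = 0.5". For anorexia nervosa (AN) it concludes "with an effect size of 0.34 and a statistical power of 0.95, we project about 40 subjects"; for Parkinson's disease (PD), "with an effect size of 0.39 and a statistical power of 0.95, we project about 30 subjects". Both effect sizes come from studies that used the affective picture set, but neither calculation says which planned measure it is for.

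**The concern.** A sample size for one test at 0.05 describes a trial with one decisive comparison per population. The analysis section describes many parallel comparisons of equal rank and one broad conclusion attached to none of them. Followed as written, with each ANOVA read at the level used for sizing, the 0.05 in the Sample size section is not the chance of a false claim of improved flexibility, and the 0.95 is not the power for a defined claim.

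What is at stake is the headline result. With no measure ranked first, the choice of which interactions carry the conclusion could be made after the results are known.

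**Working it through.** **1. The plan's own figures.** For a repeated-measures within-between interaction with two groups, m = 2 measurements and correlation ρ = 0.5, λ = f² × N × m / (1 − ρ), with 1 and N − 2 degrees of freedom.
- AN: 0.34² × 32 × 2 / 0.5 = 0.1156 × 128 = 14.7968; critical F(1, 30) = 4.1709; power 0.9609.
- PD: 0.39² × 24 × 2 / 0.5 = 0.1521 × 96 = 14.6016; critical F(1, 22) = 4.3009; power 0.9545.

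Both agree with the printed output, and 32 and 24 are the smallest even totals that reach 0.95. The sample-size arithmetic is correct for one test.

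**2. Number of tests.** Affective: 4 signals × 4 state indexes = 16. Cognitive: 1 self-report composite, taking one component. Minimum 16 + 1 = 17 per population, 34 over both. How many neuropsychological scores enter an ANOVA is not stated. Seven (TMT-A, TMT-B, ToL, three fluency scores, WCST) is an assumption and would give 24. Main effects and the planned correlations are not counted.

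**3. Chance of at least one false interaction.** Assumptions: all nulls true, each test at two-sided 0.05, no adjustment.
- Independent, 17 tests: 1 − 0.95^17 = 0.582. Over both populations: 1 − 0.95^34 = 0.825.
- Independent, 24 tests (assumed count): 1 − 0.95^24 = 0.708.
- All 17 equally correlated (simulation, 200,000 draws): 0.491 at 0.3 and 0.386 at 0.5. The two populations are separate samples, so over both: 1 − (1 − 0.491)² = 0.741 and 1 − (1 − 0.386)² = 0.623.
- Correlated only among the four indexes of one signal, 17 tests: 0.557, 0.516 and 0.458 at 0.3, 0.5 and 0.7.

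**4. Dependence on the decision rule** (independent tests, one population).
- Only interactions in the predicted direction count: 1 − 0.975^17 = 0.350.
- The composite and at least one affective index must both be significant: 0.05 × (1 − 0.95^16) = 0.05 × 0.560 = 0.028.

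**5. Power under different corrections** (noncentral F, the plan's f and ρ).

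| Total N | α = 0.025 (two primaries) | α = 0.05/17 = 0.00294 |
|---|---|---|
| AN 32 | 0.925 | 0.722 |
| AN 40 | 0.972 | 0.859 |
| AN 80 | > 0.99 | 0.998 |
| PD 24 | 0.913 | 0.678 |
| PD 30 | 0.967 | 0.831 |
| PD 60 | > 0.99 | 0.998 |

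Power of 0.95 needs total N = 36 (AN) and 28 (PD) at α = 0.025, or 52 and 40 at 0.00294. The rows for 80 and 60 apply if the projected 40 and 30 are per group, which the text leaves open.

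**The case against.** A reader might infer that a chance interaction is more likely than not in each population. The document does not support that as a flat statement. It needs near-independence: indexes taken from one recording session are likely to be correlated, and at a common correlation of 0.3 the 17-test figure is already just under one half. It also counts interactions in the wrong direction. This part of the objection stands.

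A reader might also infer that the plan tests every ANOVA at 0.05, or declares success on any single significant interaction. Neither is written. The level 0.05 appears only as a sample-size input, and the stated hypothesis is directional and joint: cognitive improvement accompanied by affective improvement. Under a strict joint rule on the composite and an affective index, the false-positive chance is below 5%. This stands too; the document does not say which rule applies.

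It can further be said that a multiplicity rule may sit in an analysis plan not shown, that a condensed article need not carry it, and that the project is largely about developing an assessment. The absence of an adjustment is therefore not the point. What remains is what the article itself fixes: per-measure testing with no measure ranked first, beside a sample size for one unidentified test. A correction over all 17 tests in a later plan would not by itself reconcile the two. If 40 and 30 are totals, power would be 0.859 and 0.831, not 0.95; if they are per group, the correction is affordable.

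**Conclusion.** The point holds in conditional form. The article plans at least 17 interaction tests per population without a hierarchy and sizes each population for one unnamed test, so the stated alpha and power do not describe the conclusion it intends to draw.

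Under unadjusted 0.05 testing with all nulls true, the chance of some false interaction ranges from about 58% per population and 83% over both (independent tests) to about 39–49% and 62–74% (common correlation 0.5 to 0.3). It falls to about 35% per population if only the predicted direction counts, and to about 3% if the composite and an affective index must both be significant. That the answer runs from 3% to 58% according to a rule the document does not state is the defect. The count of 17 follows from the text, taking one composite; any higher count rests on an assumption about the neuropsychological scores. The sample-size arithmetic itself is not in error.

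**What to change.** Before any data are examined, amend the protocol or analysis plan as follows.

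1. For each population, name two primary group-by-time interactions: the planned self-report composite, and one prespecified affective measure. A single summary over the state indexes is one option, but the investigators may prefer another; it only has to be fixed in advance.
2. Test the two with Holm at 0.05 overall within each population.
3. Report the per-signal and per-state indexes, the neuropsychological scores and the correlations as secondary or exploratory.
4. Tie the conclusion of increased cognitive and affective flexibility to the two primaries, and say whether it needs both or either.
5. State which primary each sample size refers to, and whether 40 and 30 are totals or per group.

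The cost is wording and a little power; no extra assessment is needed. At alpha 0.025, a conservative level for Holm, power per test is about 0.93 (AN, total N = 32) and 0.91 (PD, total N = 24). It is about 0.97 for both if 40 and 30 are complete totals, and above 0.99 if they are per group. These values assume that the plan's effect size applies to both primaries. Where the restated power is below 0.95, it should replace that figure. The power to show both effects together is lower than either per-test value.

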Using the proposed multidimensional assessment has the dual objective of investigating the affective, cognitive, and neurobiological components of MF, and its relationships among the different components. In general, people who exhibit greater cognitive rigidity are believed to struggle to change their emotional states: individuals who exhibit higher levels of cognitive rigidity, as assessed through self-report questionnaires and neuropsychological assessments, may demonstrate reduced variability in emotional responses (Fig 1).

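### The affective-flexibility index has no fixed direction, each possible formula reverses one of its two labels, and normalising it hides a uniform loss of variability

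*Protocol article*

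**What the plan says.** All of this is in the protocol article. The index is defined in the Statistical analysis section, in the text around Figs 4 and 5.

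- **Formula.** One sentence defines it: "calculate the reciprocal ratio between the absolute mean and variability of the signal standardized variability measures based on the inverse of Noise to Signal", with no punctuation between its two descriptions.
- **Off-diagonal entries.** "The standardized variability index is computed for each transition, considering the 30-second interval between blocks". The window runs from 15 seconds before to 15 seconds after the 120-second block boundary.
- **Diagonal entries.** "These state trait indexes are determined during the central 30 seconds of each affective block", that is, from 45 to 75 seconds.
- **Scaling.** "Normalization of transition indexes is required because the sum of transitions in Markov matrices is 1".
- **Quantity analysed.** Only the four diagonal entries are taken forward, for each person and each physiological signal. They are said to express the "probability of remaining anchored in a specific affective state (stability").
- **Hypotheses.** The Objective section treats variability as the measure of emotional flexibility and expects that more rigid people "may demonstrate reduced variability in emotional responses". The Statistical analysis section expects affective flexibility to rise in patients from T0 to T1.

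**The concern.** The diagonal is the only affective-flexibility quantity that the text says is analysed. It enters the 2x2 ANOVA (group by time) and the correlations with the cognitive and concurrent measures. The time hypothesis is directional, so a reader must know whether a larger value means more or less variability, and whether more variability in a given window means more or less flexibility. The text settles the first question nowhere, and its labels for the two kinds of window cannot both fit any one formula. The same recordings could therefore be reported as a gain or a loss of flexibility.

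A second problem is separate. Forcing the entries to sum to 1 removes a person's overall level of variability, and a lower overall level is one direct reading of the reduced variability that the Objective section predicts.

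**Working it through.** **Inputs.** The plan gives no numerical value for the index, so there is no figure of its own to reproduce. The design counts agree with one another: 13 blocks x 12 images = 156 images; 12 images x 10 s = 120 s per block; 4 states x 3 other states = 12 transitions. Each row of the 4x4 matrix thus has one central-window entry and three boundary-window entries. The variability levels below are assumed, and only their ratios matter.

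**Step 1: the two candidate formulas.** The inverse of noise-to-signal is |mean|/SD. The reciprocal of the ratio of absolute mean to variability is SD/|mean|. Each is the reciprocal of the other. The first falls with variability and the second rises with it.

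**Step 2: the labels under each formula.**

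| Formula | Diagonal, read as stability | Off-diagonal, read as passing between states |
|---|---|---|
| SD/\|mean\| | More fluctuation inside a state raises it: label reversed | More variability at a boundary raises it: label fits |
| \|mean\|/SD | A steadier signal inside a state raises it: label fits | A steadier signal at a boundary raises it: label reversed |

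**Step 3: effect on the analysed diagonal.** With row scaling, diagonal = central entry / (central entry + sum of three boundary entries). With equal windows this is 1/(1+1+1+1) = 0.25 under both formulas.

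| Change in variability | SD/\|mean\| | \|mean\|/SD |
|---|---|---|
| Boundary windows cut to 80% | 1/(1+3x0.8) = 0.294 | 1/(1+3x1.25) = 0.211 |
| Boundary windows cut to 50% | 1/(1+3x0.5) = 0.400 | 1/(1+3x2) = 0.143 |
| Central windows cut to 80% | 0.8/(0.8+3) = 0.211 | 1.25/(1.25+3) = 0.294 |
| Central windows cut to 50% | 0.5/(0.5+3) = 0.143 | 2/(2+3) = 0.400 |

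In every line the two formulas move the diagonal to opposite sides of 0.25.

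The label problem also shows from an unequal start. Under SD/|mean|, with boundary windows twice as variable as the central one, the diagonal is 1/(1+2+2+2) = 0.143. Raising central variability by half gives 1.5/(1.5+6) = 0.200, which would be read as more stable.

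**Step 4: uniform blunting.** If every window's variability is multiplied by k, every entry is multiplied by k (or by 1/k), and the factor cancels: kd/(k x row sum) = d/(row sum). For k = 0.80, 0.50 and 0.25 the normalised matrix was unchanged to machine precision under both formulas, whether scaled by row or by the whole matrix. The un-normalised mean index does move: to 0.80, 0.50 and 0.25 times its value under SD/|mean|, and to 1.25, 2 and 4 times under |mean|/SD.

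**The case against.** **The two phrases may agree.** The defining sentence is garbled. Its first half can be read loosely as |mean|/SD, which matches its second half, and a steadier signal inside a state would then raise the diagonal as the stability label requires. This has force, so the text does not prove that two contrary definitions were intended. But on that reading a quantity named a variability index falls as variability rises, and the off-diagonal label is reversed. The reversal also reaches the diagonal through the row sum: greater variability at the boundaries would raise the stability score.

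**Reduced variability is not wholly lost.** A reader might infer that the normalised index cannot register reduced emotional variability at all. The documents do not support that. Only a change proportional across the row cancels; Step 3 shows that a change in boundary relative to central variability is registered. The Objective section links rigidity to difficulty in changing emotional state, and boundary variability relative to within-state variability is a fair way to measure that. Removing the overall level is a defensible choice if it is intended and stated.

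**The diagonal has a stated meaning.** A reader might also infer that the outcome has no interpretation. It has one: a higher diagonal means stability. What is open is how the raw index maps to it.

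**What is inferred or not visible.** Row scaling is inferred from the remark about sums to 1, although whole-matrix scaling gives the same cancellation. If the diagonal were left unscaled it would show uniform blunting, but the text calls it a probability within the Markov matrix, which makes that reading unlikely. Figs 4 and 5 are not shown and may hold the formula. That could settle the direction, but not the labelling or the normalisation.

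**Conclusion.** The point holds in limited form and should be fixed before analysis. The text does not fix the direction of the index, and with one index in both kinds of window, either formula reverses one of the two labels. The consequence is a possible reversal of the conclusion: halving boundary variability takes the diagonal from 0.25 to 0.400 or to 0.143, depending on the formula. If the matrix is scaled to sum to 1, a uniform proportional loss of variability leaves no trace in the diagonal, whatever its size.

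The size of the problem in this study cannot be given. The equal starting windows and the 80% and 50% cuts are assumptions made to show direction, and the document offers no signal values from which to set a realistic range. The conclusion rests on the visible text, on the same index being used in boundary and central windows, and, for the blunting point only, on the diagonal being included in the scaling.

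**What to change.** 1. State one formula and its direction. For example, use SD/|mean| on features with a true zero, with higher meaning more variable. A true zero matters because the ratio is unstable when the mean is near zero.
2. State how the diagonal then maps to flexibility, given what that formula does in central and in boundary windows.
3. State whether scaling is by row or over the whole matrix, and that it includes the diagonal.
4. Analyse an un-normalised log index alongside the normalised diagonal, in both the 2x2 ANOVA and the correlations. Keep the mean over boundary windows and the mean over central windows separate. On the log scale the two formulas differ only in sign, because log(SD/|mean|) = -log(|mean|/SD), and a uniform halving of variability appears as a shift of ln 0.5 = -0.693 under SD/|mean|.
5. Describe the normalised entries as relative shares of variability rather than as transition probabilities. The experimenter sets the order of states, and none of the 12 planned transitions returns to the same state.

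The cost is some wording and a little extra analysis of signals already to be recorded. The drawback is that the un-normalised index keeps between-person differences in signal amplitude, so both forms should be reported. The authors' Markov diagonal need not be dropped.
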